### Intervention

#### Facility-based care

FBC will be available to all participants in this trial. Facility-based care is the care usually provided by mental health practitioners for persons with schizophrenia and their families. No guidelines or protocols are available for FBC as this is more representative of usual care in China. Psychiatrists from general or psychiatric hospitals prescribed antipsychotic medications and provide consultation, including specific information about the illness, encouragement on adherence and discussion about other specific concerns. The frequency of FBC was once per month or more, which will be determined by clinical need.

#### Community-based rehabilitation

##### Intervention development

The CBR intervention was developed through four steps that employing a range of qualitative and participatory methodologies. First, a literature review of rehabilitation and psychosocial intervention for patients with schizophrenia was conducted, resources from the World Health Organization (WHO), The Community care for People with Schizophrenia in India (COPSI) [12], Community-based Rehabilitation Intervention for people with Schizophrenia in Ethiopia (RISE) [10], etc. were reviewed to identify potential components of CBR and the likely effectiveness. Second, a scoping workshop involving psychiatrists, psychiatric nurses, community health workers and local healthcare managers was implemented to analyze the feasibility of CBR components and delivery mechanism. Third, we arranged several in-depth interviews and focus group discussions with people with schizophrenia and their caregiver and primary healthcare workers to understand the unmet needs and to evaluate the acceptability of CBR. Finally, a workshop involving CRISC director and coordinators, psychiatrists, psychiatric nursers and community health workers (potential CBR worker), local healthcare administrator and manager was conducted to synthesize the findings from step 1–3, based on which the detailed content of the intervention and the CBR training materials was developed.

Guided by previous evidence, the components of the intervention package are: 1) Structured psycho-educational information to improve the understanding of schizophrenia and address experience of illness-related stigma and discrimination; 2)proactive management of the illness to reduce medication non-adherence and improve prevention and identification of symptoms and relapse; 3) specific training strategies to improve daily life and social skills; 4) health promotion strategies to improve participants’ physical health status; 5)developing personalized rehabilitation plan to facilitate the supportive framework for participants’ further recovery and social integration.

##### CBR worker recruitment and training

Nineteen CBR workers were recruited from mental health center of the three districts in Weifang city according to the following criteria: (1) at least 12 years of schooling, (2) resident in Weifang city, (3) one-year-or-above working experience related to psychiatry or psychology and (4) interest in community work. CBR training was delivered by multiple sessions at different time (time before delivering new module) to ensure that each intervention module was fully learned and will be smoothly implemented. A intervention manual will be provided for each CBR worker. The competency of CBR workers will then be assessed using role-plays and patient vignettes.

##### CBR delivery

The CBR intervention will be delivered by group at community health centers. Two CBR workers will be attached to each sub-district and have one group of 10–20 people with schizophrenia. CBR delivery will commence immediately after recruitment into the trial. A total of 18 group intervention sessions will be implemented within the following 12 months, and each group intervention session will last 90–120 min. The intervention is delivered in two phases (Table 1): In phase 1 (intensive engagement phase), 12 intervention sessions will be delivered fortnightly during the first 6 months. The content of the intervention includes a series of modules such as developing a positive therapeutic alliance, understanding schizophrenia, adherence management, etc. (Table 1). In phase 2 (stabilizing phase), 6 intervention sessions will be delivered monthly during the last 6 months. Intervention modules in this phase are similar with phase 1 to reinforce the progress, and the content will include more in-depth discussion and address unmet needs from the first phase. In this phase, a personal rehabilitation plan for each participant will be generated to help their continued rehabilitation at home.

The content and process of the phase specific delivery of the intervention has been manualized. CBR workers will be closely supervised at each site by psychiatrists who will work as designated intervention coordinators. They will coordinate the overall delivery of the intervention and assure the quality and fidelity of the intervention at the site. The treating psychiatrists will provide clinical leadership for the community care teams and ongoing supervision to maintain safety and quality standards.

In total, we anticipate that each participant in the intervention arm will receive a maximum of 18 group-based rehabilitation sessions during the 12 months of the intervention. In evaluating the intervention, a minimum adequate number of 12 sessions attended over 12 months was set according to priori definitions.

**Table 1 Tab1:** CRISC community-based rehabilitation (CBR) intervention outline

phase	months	frequency	Objectives	CBR Modules	CBR activity
Phase 1 (intensive engagement)	1–6	fortnightly	• developing a positive therapeutic alliance • needs assessment • improving knowledge of illness • improving medication adherence • addressing familial and social difficulties	• understanding schizophrenia • psychoeducation • adherence management • physical health promotion • life skill training • social skill training • symptoms management	• warm-up exercises (15 min) • introduction & ice-breaking activity (20 min, for the first session) • sharing experience of past two weeks (30 min) • Module activity (30–40 min) • question and discussion (20 min) • assignment for next two weeks (10 min)
Phase 2 (stabilizing)	7–12	monthly	• addressing the unmet or partially met needs from the first phase • reinforcing knowledge of illness • reinforcing medication adherence • improving self-care skills • improving social interactions within and outside of the family • Generating a rehabilitation and relapse prevention plan	• psychoeducation • adherence management • physical health promotion • life skill training • social skill training • symptoms management • personal rehabilitation planning • prepare for termination	• warm-up exercises (15 min) • sharing experience of past two weeks (30 min) • Module activity (30–40 min) • question and discussion (20 min) • making rehabilitation plan (20 min) • assignment for next two weeks (10 min) • CBR summary & energetic participants awards (20 min, for the last session)

### Outcome assessment

For the primary outcome assessments, we will record the following indicators as intermediate outcome for each participant at baseline, intermediate (6 months after initiating intervention) and endline (12 months after initiating intervention) survey:

Symptoms of schizophrenia will be measured using the Positive and Negative Syndrome Scale (PANSS) [13].Personal and social function will be measured by Personal and Social Performance Scale (PSP) [14, 15].Antipsychotic adherence will be assessed using Medication Adherence Rating Scale (MARS) [16].Knowledge of illness will be measured using the Knowledge About Schizophrenia Test (KAST) [17] for each participant and their caregiver.Hospital readmission records will be extracted from electronic medical records using participants’ national identification number.

We will also be assessed the following indicators as long-term outcome for each participant at baseline and endline (12 months after initiating intervention) survey:

Physical function will be measured using Activity of Daily Living Scale (ADL) and Instrumental Activity of Daily Living Scale (IADL).Social support of participants will be measured using Perceived Social Support Scale (PSSS) [18].Quality of life of participants will be assessed using the EuroQoL five-dimensional instrument (EQ-5D) and the Schizophrenia Quality of Life Scale (SQLS) [19].The family burden of caring will be measured through participants’ caregiver interview using Burden Assessment Scale for families of the seriously mentally ill (BAS) [20].

For the secondary outcome assessment, we will calculate the cost of schizophrenia by combining the self-reported cost from participants or their caregivers and the electronic medical records. The direct cost includes inpatient during the last year and outpatient cost during the last month, which will be extracted from the electronic medical records, and self-medication cost reported by participants or their caregivers. The indirect cost includes loss of wages of caregiver, fees of transportation, accommodation and meals due to accompanying and care, and other cost during the inpatient and outpatient service utilization. All the indirect costs were self-reported by participants or their caregivers. The secondary outcome will be assessed at baseline, intermediate and endline survey. Table 2 describe the details of each outcome measure in this study.

Additionally, participants’ and their primary caregivers’ sociodemographic information, participants’ health behavior, comorbid mental and physical disorder will be recorded during the baseline survey. Participants’ family history of mental disorders, history of schizophrenia, which include the year of the first episode, current and past use of antipsychotic medication will be extracted from information system, in which all the participants were registered and recorded.

Primary care physicians will collect all data except for symptoms of illness and personal and social function. We choose primary care physicians as data collector instead of other external personnel for the following reasons: (1) typically, the primary care physicians were the doctors that in charge of the community-dwelling people with schizophrenia in their sub-district, and thus they could directly extracted the illness record of participants (after obtained the informed consent), and reduce the survey duration to prevent the occurrence of negative emotions of participants; (2) the primary care physicians were quite familiar with the people with schizophrenia in their sub-district, which may reduce the difficulties during the survey since a substantial proportion of participants have stigma issue and are reluctant to answer questions from strangers. The primary care physicians will be trained by 3 two-hour group sessions in a structured manner to ensure adequate inter-rater reliability for all scale items across the sites. The symptoms of schizophrenia and personal and social function will be assessed by psychiatrists from the mental health center of each district. A 5-hours training session of PANSS and PSP scale were provided by experts in psychiatry from Peking University Sixth hospital. All the trainees will be asked to take an examination to assess the symptom and personal and social function of one patient with schizophrenia by video. To ensure the adequate inter-rater reliability, only those who pass the exam will be qualified for the PANSS and PSP assessment in the baseline, intermediate and endline survey. Participants’ data will be either extraction from information system or collected by face-to-face interview at community health center. For participants who do not go to community health center after three invitations, a home visit will be conducted by interviewer for data collection. The survey and assessment forms will be finished by Wenjuanxing, a Chinese online platform for survey, assessment and voting.

To maintain blinding of these assessments, the primary care physicians and psychiatrists who administered the outcome measures will be independent of the CBR intervention. The primary care physicians were unable to be blinded to the allocation of treatment since they were the coordinator to contact the participants from their local sub-districts. The psychiatrists, who will assess the main primary outcomes (symptoms of schizophrenia and personal and social function), will be blinded to the allocation of treatment. Since neither the participant nor the family caregivers will be blind to their allocation status at the time of the 6 and 12 month interviews, we intend to minimize the chances of unmasking during the outcome assessments by instituting the following measures: (1) the intervention team and data collection teams at the sites will not have any interactions during the trial; (2) the data collection team are told that they are evaluating two interventions that is unknown about which one is better; (3) orient the participants and their caregivers prior to each assessment that they should not disclose whether or not they are attending CBR.

**Table 2 Tab2:** Summary of outcome measures

Outcomes (Intermediate outcome)	Interviewees	Assessment scale	Month 0 (Baseline)	Month 6 (Intermediate)	Month 12 (Endline)

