**Methods:**

This trial is a cluster randomized controlled trial design in China. The trial will be conducted at three districts of Weifang city, Shandong province. Eligible participants will be identified from the psychiatric management system where community-dwelling patients with schizophrenia have been registered. Participants will be recruited after providing informed consent. 18 sub-districts will be randomly allocated in a 1:1 ratio to facility-based care (FBC) plus CBR (intervention arm) or FBC alone (control arm). The structured CBR intervention will be delivered by trained psychiatric nurses or community health workers. We aim to recruit 264 participants. The primary outcomes include symptoms of schizophrenia, personal and social function, quality of life, family burden of caring, etc. The study will be conducted according to good ethical practice, data analysis and reporting guidelines.

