## Objectives

The objectives of the trial are: first, to examine the effectiveness of CBR as an adjunct to test the usual facility-cased care (FBC) in comparison to FBC alone in improving a range of outcomes in people with schizophrenia and their caregivers at 12 months and, second, to determine if the CBR intervention is cost effective in China.

The primary objectives of the trial are to determine whether the FBC + CBR intervention will be more effective than FBC alone in:

i)reducing symptoms of schizophrenia at 12 months;ii)improving physical function and quality of life for people with schizophrenia over 12 months, and.iii)reducing the burden of caring for caregivers of people with schizophrenia at 12 months.

The secondary objectives are to determine whether, FBC + CBR will be superior to FBC alone, in:

i)improving adherence to antipsychotic treatment at 6 months and 12 months,ii)reducing the hospital readmission rate at 6 months and 12 months for people with schizophrenia, and.iii)improving the knowledge about schizophrenia of people with schizophrenia and their caregiver at 6 months and 12 months.

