Data analysis will be conducted under intention-to-treat assumption. The primary outcome----12-month PANSS total score, adjusted for PANSS scores at baseline and site, and including clustering effects of CBR workers, will be used for examining the comparative effects of intervention and control arm. Personal and social function (PSP score), antipsychotic adherence (MARS score), knowledge of schizophrenia (KAST score) and hospital readmission will be similarly analyzed. A longitudinal analysis including both 6- and 12-month outcomes will also be performed using a GEE or random effects model including an interaction term of time and treatment allowing for modelling changes over time. Long-term outcomes (ADL & IADL, PSSS, EQ-5D, SQLS and BAS score) at 12 months will be analyzed in a similar way to the primary outcome. We will also perform residual analysis to check the data distribution and to detect outliers. Multiple imputation methods will be employed for participants with missing outcome variables.

Several sensitivity analyses are planned to be carried out. First, a complete case analysis and a complier average causal effect will be conducted. Second, a dose-response relationship between adherence to CBR intervention (number of group sessions attended) and the intermediate and long-term outcomes will be examined. Third, we will also conduct data analyses that including received quantity of different CBR modules to identify the active components. Furthermore, regression models will also be re-estimated to include possible confounders such as characteristics of CBR workers and participant characteristics that differ at baseline.

Exploratory subgroup analyses by gender, urban-rural residence, baseline symptom severity and antipsychotic adherence will be completed, although the power for these analyses has not been specifically allowed for.

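### The article contradicts itself on which outcomes are primary: one (12-month PANSS total) in the analysis section, nine rows in Table 2, and a different split in the Objectives

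*Protocol article*

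**What the plan says.** Five places in the protocol article describe the primary outcome.

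- **Data management and analysis** is the most specific. It names one outcome with a timepoint: "The primary outcome----12-month PANSS total score". PSP, MARS, KAST and readmission are to be analysed similarly, and the long-term scales along the same lines as the primary outcome. **Sample size estimation** agrees with this: it sizes the trial on PANSS total only, with alpha 0.05 and 90% power.
- **Outcome assessment and Table 2** are the broadest. The text begins "For the primary outcome assessments, we will record the following indicators as intermediate outcome for each participant" and then adds a long-term group. In Table 2 both groups sit under the primary heading, and cost of illness is the only secondary outcome.
- **Objectives** has three primary items: "reducing symptoms of schizophrenia at 12 months", "improving physical function and quality of life for people with schizophrenia over 12 months" and "reducing the burden of caring for caregivers of people with schizophrenia at 12 months". Its secondary items begin with "improving adherence to antipsychotic treatment at 6 months and 12 months" and go on to readmission and knowledge of the illness.
- **Outcome assessment, blinding paragraph**, refers to the psychiatrists "who will assess the main primary outcomes (symptoms of schizophrenia and personal and social function").
- **Abstract, Methods**, says: "The primary outcomes include symptoms of schizophrenia, personal and social function, quality of life, family burden of caring, etc".

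**The concern.** The primary label decides what the trial may conclude. Here it covers one outcome in the analysis section and nine rows in Table 2, and the Objectives draw the line between primary and secondary in a third place.

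The difference matters because the candidate outcomes are not equally well protected. Only PANSS total is powered. Only PANSS and PSP are rated by psychiatrists who are to be blinded. All other data are collected by primary care physicians, who the article says could not be blinded, and participants and caregivers know their allocation. Eight of the remaining nine measures are scales completed with participants or caregivers; the ninth, readmission, comes from medical records.

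Adherence and knowledge are also direct targets of the rehabilitation modules in Table 1. A gain on MARS or KAST with no PANSS effect could be reported as a primary success by citing Table 2, although the analysis section would make the same trial negative.

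**Working it through.** **1. The labels side by side**

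| Outcome (measure) | Objectives | Outcome assessment and Table 2 | Data management and analysis |
|---|---|---|---|
| Symptoms (PANSS) | primary | primary | the primary outcome, at 12 months |
| Personal and social function (PSP) | not named | primary | analysed similarly |
| Adherence (MARS) | secondary | primary | analysed similarly |
| Knowledge (KAST) | secondary | primary | analysed similarly |
| Readmission (medical records) | secondary | primary | analysed similarly |
| Physical function (ADL, IADL) | primary | primary | long-term outcome |
| Social support (PSSS) | not named | primary | long-term outcome |
| Quality of life (EQ-5D, SQLS) | primary | primary | long-term outcome |
| Caregiver burden (BAS) | primary | primary | long-term outcome |

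The table has nine rows and 11 measures: ten scales plus medical records. Two contradictions are firm: one primary outcome against nine rows, and three outcomes that are secondary in the Objectives but primary in Table 2.

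**2. The plan's own figure**

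The stated size is 110 per arm for PANSS total, with 90% power, alpha 0.05 and ICC 0.05. It cannot be reproduced or refuted, because neither the standard deviation nor the baseline mean is given. It can be inverted, taking a two-sided test and sub-districts as clusters:

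- cluster size: 110/9 = 12.2
- design effect: 1 + (12.22 − 1) × 0.05 = 1.56
- effective n per arm: 110/1.561 = 70.5
- implied standardised difference: √(2 × (1.960 + 1.282)² / 70.5) = 0.55

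The whole calculation belongs to PANSS at the full 0.05. No other outcome has an assumed effect and no alpha is divided, so it fits one primary outcome and not nine.

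**3. What the broad label would permit**

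Suppose each of k measures were tested at 0.05 and any one significant result counted as primary success. The article states neither condition. Under independence the family-wise error is 1 − 0.95^k:

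- k = 11 (measures): 1 − 0.569 = 43.1%
- k = 9 (rows): 1 − 0.630 = 37.0%
- k = 2 (PANSS and PSP, either sufficing): 1 − 0.9025 = 9.8%
- k = 1 (PANSS): 5%

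Scales taken on the same people will be correlated. No correlations are given, so a range was assumed and equicorrelated normal statistics simulated (400,000 draws, critical value 1.96):

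| Assumed correlation | 11 measures | 9 rows |
|---|---|---|
| 0.3 | 37% | 33% |
| 0.5 | 30% | 27% |
| 0.7 | 22% | 20% |

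**4. What it would cost to keep all 11 as primary**

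With Bonferroni, each test has 0.05/11 = 0.00455 (two-sided critical value 2.838).

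- PANSS power: Φ(3.242 − 2.838) = Φ(0.404), about 66% instead of 90%
- size for 90% power: 110 × ((2.838 + 1.282)/3.242)² = 110 × 1.615, about 178 per arm before attrition

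The 178 holds the design effect at its current value. With nine sub-districts per arm, larger clusters would raise it, so 178 is a lower figure.

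**The case against.** The strongest reply is that the analysis section already settles the matter. It names one outcome with a timepoint, the sample size uses the same scale, and describing the long-term outcomes as handled like the primary outcome sets them apart from it. That stands. It shows that the powered design is coherent and the repair is easy. It does not make Table 2 or the Objectives agree with it.

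Several stronger readings are tempting but not supported:

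- **Every outcome is tested at 0.05, and any success counts.** A reader might infer this from Table 2. The 0.05 is printed once, in the PANSS sample size calculation, and no success rule appears.
- **The missing multiplicity rule is itself an error.** Such rules are commonly left to a statistical analysis plan, which is not shown. The point here is only the contradictory labelling. An analysis plan implements the protocol's primary outcome; it does not explain why the protocol prints different ones.
- **Each of the five places is a separate contradiction.** The abstract's list is open-ended and all its named items are in Table 2. Calling two outcomes the main primary ones does not deny that others are primary. Both are loose wording, not strict conflicts.
- **43% is the trial's error rate.** It needs independence and an any-success rule. The 9.8% for two outcomes also needs either one to suffice; if both had to be significant, the error would be at most 5%.
- **Six-month testing inflates everything further.** The long-term outcomes are measured only at baseline and month 12.

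**Conclusion.** The concern holds as a contradiction in the printed text. One primary outcome in the analysis section cannot be squared with nine primary rows in Table 2. Adherence, readmission and knowledge cannot be secondary in the Objectives and primary in Table 2. Condensing a protocol into an article does not explain either conflict.

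The size is conditional. If a single significant result among the 11 measures at 0.05 were treated as primary success, the family-wise error would be about 43% under independence, and about 22% to 37% at assumed common correlations of 0.7 to 0.3. It is 5% if PANSS total at 12 months is the only primary outcome. The correlations and the any-success rule are assumptions, not statements of the article. The labelling conflict depends on neither, and it should be resolved before outcome data are examined because it fixes what may be claimed.

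**What to change.** Name the 12-month PANSS total score as the sole primary outcome in the abstract, the Objectives, the Outcome assessment section (including the blinding paragraph) and Table 2. Label every other outcome as secondary. This matches what the sample size and analysis sections already say.

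In the Objectives, reconcile physical function with the personal and social function named in the abstract and blinding paragraph. State under which objective PSP and social support fall, since neither is named there now.

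Two choices remain open to the sponsor. PSP, the other measure with blinded raters, could be a key secondary outcome tested only if PANSS is significant; this is optional. If more than one primary outcome is wanted, the article should list them, give an alpha or joint-success rule, and re-derive the power.

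With PANSS as sole primary, the sample size does not change. The cost is wording and giving up primary claims on the other scales. Whether the registry entry also needs amending cannot be judged from the article.

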**Primary outcome**					
* Intermediate outcome*					
Symptoms of schizophrenia	Participants	Positive and Negative Syndrome Scale (PANSS)	√	√	√
Personal and social function	Participants	Personal and Social Performance Scale (PSP)	√	√	√
Antipsychotic adherence	Participants	Medication Adherence Rating Scale (MARS)	√	√	√
Knowledge of illness	Participants & primary caregiver	the Knowledge About Schizophrenia Test (KAST)	√	√	√
Hospital readmission	Participants	Electronic medical records	√	√	√
* Long-term outcomes*					
Physical function	Participants	Activity of Daily Living Scale (ADL) & Instrumental Activity of Daily Living Scale (IADL)	√		√
Social support	Participants	Perceived Social Support Scale (PSSS)	√		√
Quality of life	Participants	the EuroQoL five-dimensional instrument (EQ-5D) & the Schizophrenia Quality of Life Scale (SQLS)	√		√
The family burden of caring	Primary caregiver	Burden Assessment Scale for families of the seriously mentally ill (BAS)	√		√
**Secondary outcome** Cost of illness	Participants/ Primary caregivers	Electronic medical records & self-reported self-medication cost, loss of wages of caregiver, fees of transportation, accommodation, and meals due to accompanying and care and other cost during the inpatient and outpatient service utilization	√	√	√

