#### Cost-effectiveness analysis

Direct costs of the CBR intervention will be estimated by deriving a monetary value based on actual cost. Cost of illness, as the secondary outcome will be computed based on electronic medical records & self-reported data, and then compared at intermediate line and endline. Cost-effectiveness will be assessed by calculating the incremental cost-effectiveness ratios, which will show the extra cost incurred to produce a unit improvement in symptoms, personal and social function, as well as QALYs gained at the endline. To explore the uncertainty around the estimates, cost-effectiveness acceptability curves will be derived to provide the probability of advantages for the FBC combined CBR at a range of ‘willingness to pay’ threshold levels.

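### EQ-5D is taken only at baseline and month 12 although QALYs feed the cost-effectiveness ratio, so the utility path between has to be assumed; adding EQ-5D to the existing month-6 survey is a cheap improvement

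*Protocol article*

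**What the plan says.** The Outcome assessment section of the protocol article divides the patient outcomes by schedule. PANSS, PSP, MARS, KAST and readmission are recorded "for each participant at baseline, intermediate (6 months after initiating intervention) and endline (12 months after initiating intervention) survey". Quality of life, measured by EQ-5D and SQLS, belongs to the second group: "We will also be assessed the following indicators as long-term outcome for each participant at baseline and endline" (month 12). Table 2 shows the same, with ticks for quality of life at months 0 and 12 and an empty cell at month 6.

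Cost of illness follows the three-time schedule: "The secondary outcome will be assessed at baseline, intermediate and endline survey".

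The Cost-effectiveness analysis section defines the ICER as "the extra cost incurred to produce a unit improvement in symptoms, personal and social function, as well as QALYs gained at the endline", with acceptability curves to express uncertainty. The article names no other source of utilities. The Objectives section makes cost-effectiveness the second of the trial's two overall objectives.

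Under CBR delivery, phase 1 has 12 fortnightly sessions in months 1 to 6 and phase 2 has 6 monthly sessions in months 7 to 12.

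**The concern.** A QALY gain is the area between the two arms' utility curves over follow-up. When utility is observed only at the two ends of the year, the area depends on an assumption about what happened in between. The usual choice is a straight line, which is exact only if the month-6 difference is half the month-12 difference.

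Here that is a substantive assumption, because the intervention is not evenly spread: two thirds of the sessions come in the first half of the year. The trial also visits participants at month 6 and measures almost everything else the economic evaluation uses, but not utility.

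At stake are the cost per QALY and its acceptability curve, which are the economic results most easily compared across programmes. Economic evidence for policy is one of the reasons the Background gives for running the trial. The visit schedule is protocol content: an analysis plan can choose an interpolation rule, but it cannot recover a month-6 utility that was never collected.

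**Working it through.** The article states no utility, QALY or ICER value, so there is no figure of its own to reproduce. The check sizes the effect of the missing time point.

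**Inputs from the protocol article**
- EQ-5D times: months 0 and 12 (Outcome assessment; Table 2).
- Existing survey times: months 0, 6 and 12 (Outcome assessment; Table 2).
- Sessions: 12 + 6 = 18, of which 12/18 = 67% fall in months 1 to 6 (CBR delivery).

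**Assumptions**
- No between-arm utility difference at baseline.
- m = utility difference at month 6; d = utility difference at month 12.
- Straight lines between observed points (trapezoids), time in years.
- Same incremental cost in each comparison, so the ICER changes only through its denominator.

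**Formulas**
- Two points: 1 × (0 + d)/2 = 0.5d.
- Three points: 0.5 × (0 + m)/2 + 0.5 × (m + d)/2 = 0.25m + 0.25m + 0.25d = 0.5m + 0.25d.
- They agree when 0.5d = 0.5m + 0.25d, that is, only when m = d/2.

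**Illustrative paths**

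| Path | m | Three-point gain | Two-point gain | Two-point ÷ three-point gain | Two-point ÷ three-point ICER |
|---|---|---|---|---|---|
| Gain only after month 6 | 0 | 0.25d | 0.5d | 2.00 | 0.50 |
| Linear | 0.5d | 0.50d | 0.5d | 1.00 | 1.00 |
| Full gain by month 6, then held | d | 0.75d | 0.5d | 0.67 | 1.50 |
| Peak at month 6, then partial waning | 1.5d | 1.00d | 0.5d | 0.50 | 2.00 |

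The ratios do not depend on d. For scale, with an assumed d = 0.10, the two-point gain is 0.050 QALY, against 0.025, 0.050, 0.075 and 0.100 for the four rows. At the extreme, if d = 0 but m = 0.10, two points give a gain of 0 and three give 0.5 × 0.10 = 0.050.

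**The case against.** The case against is reasonable, and much of it stands.

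- **There is no contradiction.** Text and table agree, and quality of life is deliberately classed as a long-term outcome. A reader might infer that QALYs cannot be computed from this schedule. They can; the weakness is the reliance on an assumed path.
- **Session frequency is not a utility trajectory.** A reader might infer from the front-loading that the ICER will be biased in a particular direction. The documents contain no utility data, and the paths above are chosen shapes, not predictions. Early gain that is held makes two points conservative for CBR, late gain makes them optimistic, and a linear path does no harm.
- **Month 6 is not empty.** PANSS and PSP are measured then and could inform the path. Multiple imputation is planned for missing outcomes, so it would be too strong to say that participants lost after month 6 contribute nothing to the utility analysis. They would, however, have no observed follow-up utility of their own.
- **Different visit counts for costs and QALYs are not an error in themselves.** Inpatient cost, for example, is collected with a one-year look-back.
- **Three points still interpolate.** A gain completed well before month 6 would be understated even with the added visit, so the remedy narrows the assumption without removing it.
- **Interview length matters here.** The article wants surveys kept short to spare participants distress. It does not give this as the reason for leaving EQ-5D out, but it counts against calling the addition free.

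What survives is that a utility not collected at month 6 cannot be supplied later by analysis. Surrogates and imputation inform the midpoint only through further assumptions.

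**Conclusion.** The point holds as a design weakness that is cheap to improve. The two-point EQ-5D schedule is explicit and consistent, and it leaves the QALY gain resting on an assumed path through the more intensive half of the intervention.

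In the illustrations, the two-point gain runs from half to twice the three-point gain, and the ICER from twice to half. The plateau case gives a gain 33% too low and an ICER 50% too high. These figures assume no baseline difference, trapezoidal interpolation and an unchanged incremental cost. The size and direction in this trial are unknown and may be nil.

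The scope is narrow. Only the QALY-based ICER and its acceptability curve are affected. The ratios per unit of symptoms and of personal and social function are not, and neither is the 12-month PANSS analysis. The documents do not support a wider reading that the economic evaluation as a whole is invalid.

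**What to change.** Add EQ-5D alone, without SQLS or the other long-term scales, at month 6 in the Outcome assessment text and in Table 2. Compute QALYs as the area under the utility curve over months 0, 6 and 12. Estimate the between-arm difference adjusted for baseline utility in a model that accounts for clustering.

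This also gives participants who attend month 6 and are then lost an observed follow-up utility, which can inform the planned multiple imputation.

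The cost is a few minutes more per month-6 interview. The survey exists, primary care physicians already run it, and home visits are the back-up for those who do not attend. Not everyone will be reached, since the plan allows for 20% attrition. The added time should be weighed against the wish to keep surveys short.

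If the month-6 survey has already passed, prespecify the interpolation rule and report sensitivity analyses under early-gain and late-gain paths alongside the straight line. This costs only analysis time, but it shows the uncertainty without reducing it.
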